**Figure 1 F1:**
[figure not shown]
Flowchart indicating sample randomization.

### Evaluation methods

2.6

Below is described the evaluation methods that will be used in the study.

#### Surface electromyography

2.6.1

The myoelectric signals will be collected by an electromyographer (model EMG 832C—WIFI, made by EMG System Brasil, Brazil) consisting of 8 channels with a 12-bit resolution A/D converter (Analog-digital converter), with a sampling frequency of 2000 Hz, Unit μv, Xmin-2000, Ymax 2000, Coef. A 0 and Coef. B 500, coupled to a computer.

The surface electrodes will be placed in pairs on the muscle surface of the biceps brachii muscle, accompanying the longitudinal direction of the muscular fibers. The location of the muscle surface will follow the recommendations of SENIAM (Surface Electro MyoGraphy for the Non-Invasive Assessment of Muscles). A gel-anointed type electrode will be positioned in the styloid process of the ulna of the upper limb contralateral to the limb that will be evaluated.

#### Infrared thermography

2.6.2

For the collection of infrared thermography, an infrared, FLIR model S65 camera will be used, coupled to a professional photographic tripod (1.5 meters Canon), connected to a computer with the Software Thermo Cam Researcher Professional 2.10.

The camera will be positioned 1 m away from the common image capture location of 45°, following the standardization of the emissivity parameters (0.98 of the human skin), ambient temperature 22°C (±0.9°C) and relative humidity 60%.

Five images will be captured in each group (control group, placebo group, and LLLT group):

Image 1 (basal capture) will be recorded after climatization, and in the case of the placebo group and LLLT group before the laser application;Image 2 (basal capture post LLLT) will be recorded after the laser application (placebo group and LLLT group) and before the maximal isometric voluntary contraction (MIVC);

Images 3, 4, and 5 will be recorded after the MIVC of the individual:

Image 3 will be recorded 3 minutes after MIVC;Image 4 will be recorded 15 minutes after the MIVC;Image 5 will be recorded 25 minutes after the MIVC;

Thus the capture of the images will occur before the MIVC (basal), after the LLLT (basal post LLLT), and 3, 15, and 25 minutes after the MIVC.

#### Dynamometry

2.6.3

Associated with the surface electromyography (EMG) capture, the muscle torque will be measured from the MIVC of the biceps brachii muscle for which a traction dynamometer (model DFE021115/200, EMG System do Brasil, Brazil) will be used.

The traction dynamometer will be coupled to the electromyograph. This way, the muscle strength data collection will be performed in synchronization with the myoelectric activity.

#### Visual analog scale

2.6.4

Pain intensity will be assessed by the visual analog scale (VAS) of pain which consists of a horizontal line with a scale from 0 to 10, where 0 represents absence of pain and 10 represents the worst possible pain. In this way, the volunteer will be instructed to indicate his pain intensity before and after the induction of muscular fatigue.

#### Lactate assessment

2.6.5

For the collection of blood lactate levels the Accutrend lacmeter by Roche will be used in 4 moments: before the MIVC in the traction dynamometer (baseline measurement), and 3, 15, and 25 minutes after the MIVC.

### Low-level laser therapy

2.7

The protocol for the application of LLLT will be performed through the continuous punctual transcutaneous direct method to radiate 16 points in the biceps brachii muscle with approximately 1 cm of distance between the points.

This will be done using a laser diode, with infrared λ = 808 nm, 0.028 cm^2^ of beam area, 100 mW power, a power density of 3.5 W/cm^2^, 4 Joules/point of energy, and an energy density of 142.8 J/cm^2^.

During the LLLT application all biosafety measures will be adopted, that is, all those present at the collection site will be properly equipped with safety goggles suitable to the wavelength used and the light pointer will be covered with a plastic protective film.

### Outcomes

2.8

Because this is a cross-sectional study, the outcomes will be obtained by comparing the data obtained between the groups with the aim of observing the behavior of muscular fatigue in relation to the use of LLLT, by means of the above-mentioned evaluation methods.

### Study protocol

2.9

Initially, an assessment of the individual will be carried out to analyze whether it fits into the study in question, considering the inclusion and exclusion factors already described. The individuals of the poststroke group will undergo the subjective spasticity assessment by three physiotherapists (double blind), through the modified Ashworth scale and manual evaluation of muscle strength. The term of free and clarified consent will be presented (Appendix A).

All volunteers will start in the control group and then on the second contact they undergo the study randomization as described above. The experiment procedures will be standardized in the 3 study groups according to the following sequence of events: placement of the surface electrodes in the biceps brachii muscle, climatization of the individual for 10 minutes during which the VAS and initial blood lactate measurement (baseline measurement) will be made, and after 10 minutes of air conditioning image 1 will be captured by means of infrared thermography.

To perform the muscular fatigue induction protocol of the biceps brachii muscle, the individual will be positioned at the Scott bench with the elbow at 45°. An inelastic band will have 1 of its fixed extremities in the traction dynamometer and the other end positioned on the forearm of the volunteer to perform the MIVC protocol of the brachii biceps muscle.

The protocol consists of 3 MIVCs during 50 uninterrupted seconds with an interval of 50 seconds between each contraction. During the contractions the myoelectric activity and muscular strength will be collected synchronically.

The assessments after the MIVC will be performed at three distinct moments (3, 15, and 25 minutes) following the same sequence of events: capture of the image by means of infrared thermography (images 3, 4, and 5) and blood lactate measurement.

The placebo group and the LLLT group will first undergo the climatization for 10 minutes, VAS application, blood lactate measurement (baseline measurement), image 1 capture by means of infrared thermography and LLLT application. After 3 minutes, the capture of image 2 will be performed by infrared thermography, and the surface electrodes will be positioned in the biceps brachii muscle. Subsequent events were the same as above.

For a better visualization of the sequence of events of the study a flowchart was made as shown in Fig. 2.

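### Sessions described as standardised differ in electrode order and pre-exercise time, and the text conflicts on image 2 in control; this confounds contrasts with control but not LLLT versus placebo

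*Protocol article*

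**What the plan says.** Section 2.9 (Study protocol) opens with a sequence meant for all three conditions: "The experiment procedures will be standardized in the 3 study groups according to the following sequence of events: placement of the surface electrodes" on the biceps, then "climatization of the individual for 10 minutes during which the VAS and initial blood lactate measurement (baseline measurement) will be made", then image 1, then the fatigue protocol.

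Later, the same section gives two of the conditions a different start: "The placebo group and the LLLT group will first undergo the climatization for 10 minutes, VAS application, blood lactate measurement (baseline measurement"), image 1 and the laser application. It continues: "After 3 minutes, the capture of image 2 will be performed by infrared thermography, and the surface electrodes will be positioned" on the biceps. From there the steps are said to match the first sequence.

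Section 2.6.2 (Infrared thermography) says: "Five images will be captured in each group (control group, placebo group, and LLLT group"). Its definition of image 2, however, is that it "will be recorded after the laser application (placebo group and LLLT group) and before the maximal isometric voluntary contraction". No equivalent moment is given for control.

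Section 2.3 (Groups) describes control as having no laser and placebo as the same application with the device off. Section 2.5 (Randomization and blinding) puts control first for everyone and randomises only the order of placebo and LLLT. Section 2.8 (Outcomes) says that outcomes come from comparing the groups and singles out no contrast.

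**The concern.** The two sequences in section 2.9 cannot both apply to all three conditions. If the text is followed literally, control differs from the other two in more than the absence of a laser, and it does so in the same way for every participant. No analysis can then separate the procedural difference from the effect of the condition.

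Two of the three pairwise contrasts involve control. Placebo versus control would ordinarily show what the sham handling does by itself. Here it also carries a longer wait before exercise and a different skin surface at the first image. LLLT versus control carries the same two differences on top of the laser. The outcomes most exposed are thermography and change in lactate from baseline, because both use a pre-exercise reading as reference.

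The image count is a separate conflict: the reader cannot tell whether control yields four images or five.

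**Working it through.** **The sequences side by side (section 2.9)**

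| Step | Control (first sequence) | Placebo and LLLT |
|---|---|---|
| 1 | Electrodes on | Climatisation, 10 min, VAS, lactate |
| 2 | Climatisation, 10 min, with VAS and lactate | Image 1, no electrodes yet |
| 3 | Image 1, electrodes on | Laser on or off |
| 4 | – | 3 min, then image 2 |
| 5 | – | Electrodes on |
| 6 | Contractions | Contractions |
| 7 | Image and lactate at 3, 15, 25 min | Image and lactate at 3, 15, 25 min |

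**Electrodes.** Images 3 to 5 follow electrode placement in all three conditions. The change from image 1 to those images therefore spans electrode placement in placebo and LLLT, but not in control.

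**Time before exercise.** The documents give no duration for the laser application, so it has to be derived from section 2.7: 16 points, 4 J per point, 100 mW, beam area 0.028 cm². The stated densities were checked first:

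- energy density: 4 / 0.028 = 142.86 J/cm² (stated 142.8)
- power density: 0.1 / 0.028 = 3.57 W/cm² (stated 3.5)

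The inputs agree with each other apart from truncation. Then:

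- time per point = energy / power = 4 J / 0.1 W = 40 s
- 16 points in turn = 16 × 40 = 640 s = 10.67 min
- plus the stated wait: 10.67 + 3 = 13.67 min

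From the start of climatisation to exercise this gives about 10 min in control and 10 + 13.67 = 23.67 min in the other two, before any time for electrode placement and positioning.

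Two assumptions are needed that the documents do not state: points are treated one at a time, and sham lasts as long as active. Varying the first:

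| Points treated at once | Laser time | Extra time including 3 min wait |
|---|---|---|
| 1 | 640 s | 13.67 min |
| 2 | 320 s | 8.33 min |
| 4 | 160 s | 5.67 min |
| 16 | 40 s | 3.67 min |

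If sham were shorter than active, the placebo gap would be smaller, but not below the stated 3 min. For image 1 the gap is direct, since that image follows the 10 min in every session. For lactate it also assumes that the baseline sample is taken at the same point relative to image 1; the first sequence only places it within the 10 min.

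**Images.** Section 2.6.2 promises five per condition. In control, its definitions yield images 1, 3, 4 and 5, which is four, and section 2.9 adds no image 2 for control.

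**The case against.** The strongest reply is that the contrast that isolates the laser is sound. LLLT and placebo follow one sequence, placebo is the same application with the device off, and their order is randomised. The contraction protocol and the 3, 15 and 25 min readings are common to all three sessions. Electromyography and torque are recorded during the contractions, so the order of electrodes and image 1 does not bear on them. All of this stands. A reader might infer that control is not comparable at all, or that the trial cannot assess the laser; the documents support neither.

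A reader might also infer that image 2 has no comparator. It has one: the placebo session supplies it, with the same handling and wait. Nor is it settled that control has no image 2. The text contradicts itself, and Figure 2, which is not shown here, may settle it. A figure would not remove the conflicting sentences.

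The text could be read charitably as a general sequence with an exception for two conditions. That softens the wording conflict, but the difference in procedure remains.

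The 13.7 min is derived, not stated, and rests on assumptions; this is accepted, and a range is given. The documents also give no figure for how far skin temperature or lactate would move over such an interval, so the size of the bias is unknown. The protocol does, however, require climatisation and a room held at 22°C (±0.9°C), which treats skin temperature as sensitive to the surroundings.

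Finally, section 2.9 does not list a pain rating after exercise, although section 2.6.4 has volunteers "indicate his pain intensity before and after the induction of muscular fatigue". That is condensed text, not a contradiction, and is not counted here.

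**Conclusion.** The point holds for contrasts with control. Section 2.9 contradicts itself on electrode order, and section 2.6.2 contradicts itself on the number of images in control. Followed as written, control has a different skin surface at image 1. It also has a baseline-to-exercise interval shorter by at least 3 min, and by about 3.7 to 13.7 min once laser time is added under the equal-sham assumption. This confounds two of the three pairwise contrasts, mainly for thermography and change in lactate. The direction and size of the resulting bias cannot be worked out from the documents.

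The randomised comparison of LLLT with placebo is untouched by this.

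A reader might infer that matching the sequences would make control a clean comparator. It would not. Control is always the first, non-randomised session, so its contrasts stay confounded with session order whatever the procedure.

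**What to change.** Write one sequence for all three sessions: climatisation with VAS and lactate; image 1 before electrodes; an intervention slot of equal length (laser on, device off, or no laser in control); 3 min; image 2; electrodes; contractions; then the existing 3, 15 and 25 min readings. State the length of the slot and that sham lasts as long as active. Reconcile sections 2.6.2 and 2.9 so that image 2 is defined in all three conditions and the count of five is true in each.

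State as well that LLLT versus placebo carries the conclusion about the laser, and that contrasts with control are descriptive because control always comes first.

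The cost is up to about 14 min more per control session. Over 60 participants that is at most 60 × 13.67 = 820 min, or about 13.7 hours, with no new equipment or staff.

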**Figure 2 F2:**
[figure not shown]
Flowchart demonstrating the study protocol. EMG = surface electromyography, LLLT = low-level laser therapy, MIVC = maximal isometric voluntary contraction, VAS = visual analog scale.

### Statistical analysis

2.10

To assess the effects of LLLT, normality tests will be applied which allow the selection of a more adequate statistical test to perform the intra and intergroup comparisons. Statistical significance will be adopted as *P* < 0.05. The data and results will be presented through tables and graphs. Scientific Data Analysis and Visualization (SciDAVis, USA) will be the software of choice.

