### Study design

2.2

This is a cross-sectional, comparative, randomized, placebo, and double-blind clinical trial. Thirty healthy individuals and 30 individuals with after effects of spastic hemiparesis of both sexes will be recruited, totaling 60 individuals. The study will be divided into 2 phases, with phase I being performed with healthy individuals and phase II performed with individuals with spastic hemiparesis. The study will be carried out at the Laboratório de Engenharia e Reabilitação Sensório Motora, belonging to the Instituto de Pesquisa & Desenvolvimento of Universidade do Vale do Paraíba (Brazil).

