### Randomization and blinding

2.5

All individuals (phase I and phase II) will go through all the study groups (control group, placebo group, and LLLT group) with a minimum interval of 7 days between them; however, all individuals will initiate the protocol in the control group.

The randomization of the sample will be performed in the second session in which the individuals will be divided into two classes: class A and class B. Individuals who draw class A will start in the placebo group and finalize in the LLLT group, whereas individuals who draw class B will start in the LLLT group and subsequently perform the placebo group, making it a cross study.

Researcher 1 will be responsible for the instrumentation of the LLLT apparatus, whereas researcher 2 will be responsible for analyzing the data. Only researcher 1 will know in which group the individual will be allocated, and the type of treatment used will be hidden from researcher 2 and the participant. Figure 1 shows the flowchart indicating the randomization of the sample.

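### Normality tests on the trial data choose the analysis, and neither of the usual tests they would choose between adjusts for session in the placebo/LLLT crossover

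*Protocol article*

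**What the plan says.** The protocol article, section 2.10 (Statistical analysis), gives one rule for choosing the analysis: "normality tests will be applied which allow the selection of a more adequate statistical test to perform the intra and intergroup comparisons". The threshold follows: "Statistical significance will be adopted as" P < 0.05. The section names no normality test and no candidate tests. It does not say whether raw readings, within-person differences or residuals are to be tested for normality.

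The design to be analysed is set out elsewhere in the article:

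- **Sample (2.2):** "Thirty healthy individuals and 30 individuals with after effects of spastic hemiparesis of both sexes will be recruited, totaling 60 individuals". Healthy people form phase I and people with spastic hemiparesis form phase II.
- **Sessions (2.5):** each person has three, "with a minimum interval of 7 days between them; however, all individuals will initiate the protocol in the control group".
- **Order (2.5):** "Individuals who draw class A will start in the placebo group and finalize in the LLLT group"; class B takes the two in the reverse order. The ratio of class A to class B is not stated.
- **Lactate (2.6.5):** "before the MIVC in the traction dynamometer (baseline measurement), and 3, 15, and 25 minutes after the MIVC".
- **Pain (2.6.4):** "the volunteer will be instructed to indicate his pain intensity before and after the induction of muscular fatigue".
- **Thermography (2.6.2):** five images per session, the first before any laser application.
- **EMG and torque (2.6.3, 2.9):** recorded during the contractions; no pre-contraction reading is described.

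**The concern.** Two things follow from the rule as written.

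First, the hypothesis under test depends on the data. A mean-based test and a rank-based test do not ask the same question. Lactate may go one way and temperature another, the 3-minute reading one way and the 25-minute reading another, or phase I one way and phase II another. The Conclusions section sets out to compare the effects in healthy and spastic muscle, and that comparison is harder to read if the two phases were analysed by different tests.

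Second, the rule directs attention to the shape of the distribution, whereas the feature of this design that matters more is the session. LLLT and placebo are compared across sessions 2 and 3, in an order that differs by class. Any learning, familiarisation or residual fatigue between those sessions enters each person's LLLT–placebo difference, with one sign in class A and the opposite sign in class B. A plain paired t test and a Wilcoxon or Friedman test both leave it there, so whichever way the normality test falls, the session effect is not removed. What is at stake is power, and bias as well if the classes are unequal in size.

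**Working it through.** The article gives no effect size, SD, power or distribution, so it has no figure to reproduce. Inputs from the article are n = 30 per phase, two sequences and a 0.05 level (two-sided assumed). Everything else below is an assumption.

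**1. How often would the gate switch tests?** Simulated Shapiro–Wilk rejection at 0.05, n = 30, log-normal readings, within-person correlation 0.5 to 0.8:

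| Coefficient of variation | Raw readings | Paired differences | Log differences |
|---|---|---|---|
| 0.2 | 19% | 8% | 5% |
| 0.3 | 34–36% | 13–14% | 4–5% |
| 0.5 | 68% | 29–32% | 5–6% |
| 0.8 | 92–93% | 56–59% | 5% |

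The answer depends on the unknown distribution and on which quantity is tested. The article gives neither.

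**2. Does the gate inflate type I error?** The rule simulated was: Shapiro–Wilk on the LLLT–placebo differences, then paired t if not rejected and signed-rank if rejected. With no session effect, type I error was 4.6–5.2% over normal and skewed data and class splits of 15:15, 18:12 and 20:10. No inflation is visible.

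**3. What does ignoring session cost?** Let the within-person difference have SD 1, the LLLT effect be τ = 0.53, the session effect (session 3 minus session 2) be π, and the classes be 15:15. The LLLT–placebo difference then has mean τ + π in class A and τ − π in class B.

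*Unadjusted paired t.* The mean difference is still centred on τ, with true SE √(1/30) = 0.183. The pooled sample variance, however, is expected to be 1 + π² × 30/29. Taking that as the estimated variance, with a t critical value of 2.045 on 29 df:

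- π = 0: cut-off 2.045 × √(1/30) = 0.373; z = (0.53 − 0.373)/0.183 = 0.86; power about 80%.
- π = 0.5: variance 1.259; cut-off 2.045 × √(1.259/30) = 0.419; z = 0.61; power about 73%.
- π = 1: variance 2.034; cut-off 2.045 × √(2.034/30) = 0.533; z = −0.01; power about 49%.

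*Period-adjusted t.* Compare the session 3 minus session 2 differences between the classes. Their means are π + τ and π − τ, so π cancels and the contrast is 2τ = 1.06. The SE is √(1/15 + 1/15) = 0.365, and the cut-off on 28 df is 2.048 × 0.365 = 0.748. Then z = (1.06 − 0.748)/0.365 = 0.86, and power is about 80% whatever π is.

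Simulation (3,000 runs each) agrees and adds the rank tests:

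| Session effect | Paired t | Wilcoxon | Period-adjusted t | Period-adjusted rank-sum |
|---|---|---|---|---|
| 0 | 80% | 78% | 80% | 77% |
| 0.5 SD | 73% | 70% | 80% | 77% |
| 1 SD | 49% | 42% | 79% | 74% |

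**4. Unequal classes.** With a 20:10 split and π = 1, the unadjusted mean difference is biased by π × (20 − 10)/30 = 0.33 SD. Simulated type I error is about 18% for the paired t alone and about 18.5–19% for the gated rule. The two period-adjusted tests stay at about 4–5%. The error therefore comes from ignoring session; the gate adds almost nothing to it.

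**5. Can control join the same model?** Control is session 1 for everyone, so over three sessions LLLT indicator + placebo indicator = session 2 indicator + session 3 indicator. Fitting condition and session together is rank-deficient. Only the LLLT–placebo contrast, from sessions 2 and 3, can be separated from session.

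**The case against.** The strongest reply is that this is a condensed article. Candidate tests, model terms and the handling of period commonly sit in the full protocol or analysis plan, and their absence here is no finding. That stands for what is merely unsaid. It does not cover the rule that is stated: the article fixes test selection by normality testing, and a later plan that only named the tests would keep that rule.

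A reader might also infer several stronger points that the article does not support:

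- *That the gate invalidates the P values.* The check in step 2 shows no visible inflation.
- *That the analysis will tend to move to rank tests.* The article names no rank test and gives no distribution. A switch is plausible for skewed raw readings or pain scores near zero, and uncommon for paired differences at low variability.
- *That about half of trials would switch.* Lactate has 3 conditions × 4 times = 12 sets of readings per phase, and 1 − 0.95¹² = 46% is the chance, for independent tests on normal data, that at least one is rejected. Nothing in the article says that one rejection changes the LLLT–placebo test.
- *That rank tests are at fault because they cannot adjust.* A rank-sum test on period differences adjusts for session, and rank analysis of covariance can take a baseline. The paired t test ignores session just as the signed-rank test does.
- *That the crossover structure is lost.* Signed-rank and Friedman tests keep the within-person pairing; what they omit is session.
- *That results could not be set side by side.* Different tests do not by themselves prevent the reporting of comparable estimates.

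**Conclusion.** The point holds in a limited form. Section 2.10 makes the choice of test depend on the trial data, so the hypothesis tested may differ between outcomes, time points and phases. The usual tests on either branch leave session unadjusted in a design whose order of treatment varies by class. How often the test would switch cannot be known from the article: at an assumed coefficient of variation of 0.3 it is about 35% on raw readings, 13–14% on paired differences and about 5% on log differences.

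The material loss is power, and it arises from ignoring session: nothing if there is no session effect, about 7 percentage points for the paired t at 0.5 SD (80% to 73%), and about 30 at 1 SD (79% period-adjusted against 49%). These figures rest on an assumed effect of 0.53 SD, equal classes and assumed session effects, none of which the article gives. The point is worth acting on because the change is cheap and uses data already being collected.

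**What to change.** Replace the normality sentence in section 2.10 with a pre-specified analysis:

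1. Within each phase, and for each outcome, estimate LLLT minus placebo from sessions 2 and 3 only. Use a mixed model with condition, session and class as fixed effects and participant as a random effect, and report the estimate with its confidence interval.
2. Add the session baseline as a covariate where one is measured before the laser: lactate, thermography (image 1) and pain. Omit it for EMG and torque.
3. Analyse lactate on the log scale, decided in advance.
4. Check residuals. As a sensitivity analysis that does not replace the main result, report a rank-sum test of the within-person session 3 minus session 2 differences, class A against class B.
5. Report contrasts with control as descriptive, since control cannot be separated from session 1.

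The cost is a few sentences and slightly more analysis work. No new data are needed. Section 2.10 names SciDAVis as the software; confirm that it can fit the model, or name a package that can.
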